### Intervention description {11a}

Participating girls will be randomly distributed into two subgroups (1:1):Mini-spiomet subgroup: girls will swallow a half-dose of the SPIOMET tablet once daily at dinner time, for 12 months. SPIOMET is a fixed-dose combination within a single tablet containing the active pharmaceutical ingredients spironolactone (50 mg), pioglitazone (7.5 mg), and metformin (850 mg), developed according to the formula that has been tested in a phase 2a trial in adolescents with PCOS [6] and is currently tested further in a multicenter, double-blind, placebo-controlled phase 2b trial that is funded through the EU’s Horizon 2020 programme (899671-SPIOMET4HEALTH) and is endorsed by the European Medicines Agency (EMA) via an approved Paediatric Investigation Plan (PIP; P/150/2021). The proposed excipients are povidone (polyvinylpirrolidone) k-30, microcrystalline cellulose, croscarmellose sodium, polyglykol 4000 PS, magnesium stearate and purified water.Placebo subgroup: girls will swallow a similar tablet (at similar timing and for a similar duration) containing only the aforementioned excipients.

The tablets containing placebo and those containing the active ingredients (SPIOMET) will have a score line to facilitate the split into two halves immediately before intake, will have the same size, shape and color, and will thus be indistinguishable from one another, to ensure the double-blind nature of the study.

### Criteria for discontinuing or modifying allocated interventions {11b}

In all participating girls, safety markers [blood count, circulating levels of alanine transaminase (ALT), aspartate transaminase (AST), gammaglutamyltransferase (GGT), thyroid-stimulating hormone (TSH), urea, creatinine, electrolyte panel, vitamin B12, folic acid] will be assessed at treatment start, after 6 months and 1 year on treatment, and after 1 year off treatment, as well as upon reporting any adverse events. Glucose blood levels <65 mg/dL and a progressive increase of creatinine, urea, transaminase or potassium levels, will be a reason for discontinuing the medication. In addition, the existence of signs and/or symptoms of hypoglycemia, the appearance of a persistent skin rash, abdominal pain, persistent nausea and/or vomiting, headaches, sinusitis, and severe bacterial infections, will be also a reason for discontinuation. In those cases, hepatic and renal function will be periodically monitored until the disappearance of the symptoms or the normalization of the altered parameters.

### Strategies to improve adherence to interventions {11c}

Participating girls will be contacted every 3 months — either in person within a medical visit or by phone — to maintain a close contact with them, and to monitor adherence and adverse events.

Adherence to treatment will be screened by history at each clinical visit and by tablet counts in the pharmacy dispensing the study medications (ratio between the number of tablets prescribed and dispensed for the period between two hospital appointments and the number of half tablets returned by the patient at the following appointment).

### Relevant concomitant care permitted or prohibited during the trial {11d}

Girls who participate in this trial cannot participate in another trial at the same time.

Permitted concomitant treatments:Acetaminophen.

Prohibited concomitant treatments:Anticoagulants, anti-inflammatory medications, (other) oral hypoglycemic drugs, (other) anti-androgens, estrogens, progestogens, digoxin;Potassium-sparing diuretics, as well as supplements or food complements based on it;Oral contraceptives throughout the duration of the study;Iodinated contrast agents; andCaution should be taken with the concomitant use of drugs that can cause hyperkalemia or metabolic acidosis, such as non-steroidal anti-inflammatory drugs, including selective cyclooxygenase II inhibitors, angiotensin-converting enzyme inhibitors, receptor antagonists of angiotensin II and diuretics, especially loop diuretics.

### Provisions for post-trial care {30}

Each of the participating centers holds a specific insurance for patients participating in clinical trials.

### Outcomes {12}

#### Primary outcome

The primary outcome is annualized bone age (BA) advancement over the on-treatment year. A hand and wrist X-ray of the left hand will be obtained at the treatment start and after 1 year on treatment. BA advancement will be measured by an automated/blinded method called BoneXpert (Visiana, Denmark) [1].

#### Secondary outcomes

◦ Clinical variables: weight, height, BMI, waist and hip circumference and their ratio (WHR), systolic blood pressure (SBP), diastolic blood pressure (DBP), and Tanner stage [4].◦ Endocrine-metabolic variables:fasting glucose, insulin, HOMA-IR [5], IGF-ILH, FSH, testosterone, androstenedione, SHBG, FAI and estradioltriglycerides; total, low- and high-density lipoprotein (LDL and HDL) cholesterolultra-sensitive C-reactive protein (usCRP), GDF-15, HMW-adip, CXCL14.◦ Safety markers: blood count, circulating concentrations of alanine transaminase (ALT), aspartate transaminase (AST), gammaglutamyltransferase (GGT), thyroid-stimulating hormone (TSH), urea, creatinine, electrolyte panel, vitamin B12, folic acid.◦ Abdominal fat partitioning (subcutaneous visceral area) and intrahepatic fat by MRI.◦ Dietary habits, tablet acceptability, study adherence, adverse events.

### Participant timeline {13}

Figure 1 depicts the diagram of the study design.

**Fig. 1 Fig1:**
[figure not shown]
Diagram of the study design

### Sample size {14}

In a previous study performed in girls with a history of low-BW and rapid postnatal catch-up in weight, metformin treatment for 4 years (425 mg for 2 years, then 850 mg for 2 years) slowed down the accelerated bone maturation [38]. The progression of bone maturation, as assessed by the mean ratio of Δ BA over Δ CA, was faster in untreated girls [≈1.20 ± 0.2 (SD)] as compared to metformin-treated girls [≈1.00 ± 0.2 (SD)] (*P*≤0.05). To obtain a significance level of 0.05% and power of 90%, a total of 42 girls (21 in each study arm) must be included to detect the minimal relevant difference in bone age progression (1.20 vs 1.00 years) (https://clincalc.com/stats/samplesize.aspx). The number of patients has been further increased (*n*=32 in each study arm) to guarantee the necessary sample size, in the case up to one third of the participants drop out of the study.

### Recruitment {15}

Candidate girls will be recruited at the Outpatient Clinic of HJT and HSJD among those referred by pediatricians of primary care for early onset of puberty. Confirmation of eligibility will require a clinical visit where inclusion and exclusion criteria will be carefully screened. A baseline blood test will be performed to assess circulating concentrations of 17-hydroxyprogesterone (17-OHP) in order to rule out congenital adrenal hyperplasia due to 21-hydroxylase deficiency or abnormal thyroid, kidney, or liver function, all of which are exclusion criteria. If a girl meets all the inclusion criteria and none of the exclusion criteria, she will become eligible to participate in the study, the objective of which will then be explained so that written informed consent can be obtained from at least one parent or legal guardian.

## Assignment of interventions: allocation

### Sequence generation {16a}

Patients will be randomized using Stratified Permuted Block Randomization. Trial participants will be subdivided into strata, and then permuted block randomization will be used for each stratum. A block randomization list with 4 randomization blocks will be created. Each block will include 8 patients. There will be a randomization list per center and the total number of subjects per center will be 32 patients (4 blocks x 8 patients/block) with a final distribution of 16 patients who will receive mini-spiomet and 16 who will receive placebo at each center.

BLOCK 1: Medication: mini-spiomet vs placebo

BLOCK 2: Chronological age (CA): 7.7≤ CA≤8.4 years vs 8.5 ≤ CA ≤9.3 years

BLOCK 3: Birth weight (BW-SDS, in standard deviations by sex and gestational age):−2.5 ≤ BW-SDS <−1.036 (15th percentile)−1.036 ≤ BW-SDS ≤ 0 (33rd percentile)

BLOCK 4: Body mass index (BMI-SDS, in standard deviations by sex and chronological age at the clinical visit):0 ≤ BMI-SDS ≤ +1.036 (85th percentile)+1.036 < BMI-SDS ≤ +2.5 (97th percentile)

### Concealment mechanism {16b}

A randomization list per center will be generated using the program Blockrand: Randomization for Block Random Clinical Trials R package; version 1.5; Published: 2020; Author: Gdreg Snow; https://CRAN.R-project.org/package=blockrand. Patients will be sequentially allocated to a group by the pharmacy service of each center.

### Implementation {16c}

Upon receipt of informed consent (see above), study participants will be enrolled by the recruiting investigator, usually a pediatric endocrinologist, and will be assigned a center-specific registration number that will appear as HSJD-miniSPIOMET-number or HJT-miniSPIOMET-number; this unique number will be used to identify each participant throughout the study. Subsequently, the hospital pharmacy will receive the information that will allow for randomization and for delivery of the allocated medication.

## Assignment of interventions: blinding

### Who will be blinded {17a}

Throughout the on-treatment phase, the pharmacy at each center will be the sole entity with knowledge on treatment allocation.

After locking the on-treatment data base, the statistically involved investigators will be unblinded in order to allow for data analysis. The statistical analyses will be performed by independent investigators who will have no contact with the patient or with the clinical investigators.

Study participants and clinically involved investigators will remain blinded until the end of the post-treatment year.

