**Methods:**

Randomized, placebo-controlled, multicenter, phase 2a, study in 64 girls [age, 8.0–9.5 years; birthweight (BW) for gestational age: −2.5 < *Z*-score <0, body mass index (BMI): 0 < *Z*-score < +2.5 and early progressive puberty (Tanner B2 at 7.7–9.3 years)]. Pharmacological intervention will be with a half-dose version of SPIOMET (mini-spiomet), a combination that reverts the PCOS phenotype in “mismatch” adolescents; mini-spiomet will contain spironolactone (25 mg/day, to raise brown adipose tissue activity), pioglitazone (3.75 mg/day, to raise adiponectin and insulin sensitivity), and metformin (425 mg/day, to raise AMPK activity and GDF15). Recruitment: 1 year; double-blind treatment: 1 year; open follow-up: 1 year; analyses and reporting: 1 year. Interventions: randomization (1:1) for placebo *vs* mini-spiomet. *Primary outcome*: annualized bone age advancement (0–1 year) by BoneXpert; *secondary outcomes*: insulin, IGF-I, high-molecular-weight adiponectin (HMW-adip), sex hormone binding globulin (SHBG), ultra-sensitive C-reactive protein (usCRP), androgens, luteinizing hormone (LH), follicle-stimulating hormone (FSH), oestradiol, growth-and-differentiation factor 15 (GDF15), C-X-C motif chemokine ligand-14 (CXCL14), safety parameters, and quantification of hepato-visceral fat.

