#### Reduction of ectopic fat in “mismatch” girls with accelerated maturation and in adolescents with PCOS: pilot studies

Previous pilot studies performed by our group in rapidly maturing mismatch girls with precocious pubarche and/or early puberty have disclosed that metformin in monotherapy over a period of 3–4 years (up to 850 mg/day), can reduce central adiposity in viscera and liver [35–37], slow down bone maturation [38], delay pubertal onset [39], and decelerate the progression of puberty to menarche [40, 41] and to adolescent PCOS [42], while augmenting height gain [40, 41]. In mismatch adolescents with PCOS, a low-dose combination of spironolactone (50mg), pioglitazone (7.5mg), and metformin (850mg) in three separate tablets (SPIOMET) was recently shown to be capable of reversing the entire PCOS phenotype after only 1 year of treatment, including menstrual irregularities, hyperandrogenemia, and insulin resistance, through decreasing hepato-visceral fat excess [43–46]. Here, we propose to conduct a randomized, placebo-controlled, multicenter study using only half of the SPIOMET tablet, i.e., with half-dose spiomet (mini-spiomet: spironolactone 25mg; pioglitazone 3.75mg; metformin 425mg). Administering a triple combination instead of metformin in monotherapy will allow to decrease the dose of each component and to reduce the treatment period to 1 year. The rationale for using three different medications is that each of those medications targets a distinct mismatch-derived dysfunction.

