*Metformin* has pleiotropic effects but is generally considered to serve as a net “insulin sensitiser” in conditions of ectopic adiposity with insulin resistance; in addition, it raises AMPK activity, and the circulating concentrations of Growth-and-Differentiation Factor 15 (GDF15), a peptide hormone that reduces hepatic steatosis and raises intestinal glucose utilization thereby promoting weight loss [59–61]. Metformin was first approved in 1959, and since then several FDCs have been approved for the treatment of type 2 diabetes as first- and/or second-line therapies [62]. Worldwide, metformin is the drug most widely prescribed for the treatment of type 2 diabetes in adults and in children older than 10 years; its use has significantly increased in younger children and adolescents without diabetes, including for early maturation and PCOS in girls [37–41, 63]. Extensive experience has been gathered over the last 60 years related to the clinical use and safety of metformin [64]. In 2001, the European Medicines Agency (EMA) issued a favorable benefit-risk ratio for metformin that outlines its safety in humans [62]. The main side effects are gastrointestinal symptoms (~10%), that usually resolve after therapy start [64]. Lactic acidosis has been only described in cases of renal, cardiac and hepatic failure, or after intentional overdose [65]. A decrease of vitamin B12 serum levels may occur after long-term treatment but appears to be of no clinical relevance [66]. The combination of spironolactone and metformin is not associated with a higher incidence of adverse events compared to low-dose spironolactone or metformin in monotherapy [50]. Based on the EMA Summary of Product Characteristics (https://www.medicines.org.uk/emc/product/594/smpc#POSOLOGY), the dose range studied for metformin in clinical trials is mainly 200–850 mg/day, with a maximum of 2000 mg/day. Hence, the proposed dose of metformin (425 mg/day) will be in the lower recommended range, assuming that the weight of pubertal girls aged 8–9 years will be >25 kg [67].

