### Trial design {8}

The mini-spiomet trial is designed as a double-blind, randomised, controlled, parallel-group, two-arm, superiority, multicenter phase 2a trial with 1:1 allocation ratio. Girls will be randomly assigned to receive daily either placebo (*n*=32) or a low-dose combination of three generics within a single tablet, namely mini-spiomet (spironolactone 25 mg + pioglitazone 3.75 mg + metformin 425 mg; *n*=32) for 1 year. After this year, all girls will be followed for 1 year. Halfway the subsequent year, all girls will be contacted for information on menarche.

Girls will be randomized (1:1) in blocks, according to age, birthweight (BW), and BMI. The study will test the effects of mini-spiomet (*vs* placebo) on bone maturation, endocrine-metabolic and inflammation variables and abdominal fat distribution, both on- and post-treatment.

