## Data collection and management

### Plans for assessment and collection of outcomes {18a}

#### Collection of outcomes

*Baseline evaluation (time 0):* will include the clinical visit to collect clinical variables: height, weight, BMI, Tanner stage, waist and hip circumference and their ratio (WHR), SBP, DBP, a hand and wrist X-ray (to assess bone age), MRI (to assess abdominal fat partitioning and hepatic fat) and blood sampling in the fasting state (to assess endocrine-metabolic and inflammation variables and safety markers). Dietary habits will be also recorded through a standard questionnaire (Kidmed).

*Evaluation on treatment (time 6 months and 1 year):* a clinical visit with the same parameters collected at baseline, an abdominal MRI, and a blood sample extraction (to assess endocrine-metabolic and inflammatory variables and safety markers) will be performed after 6 months and after 1 year on treatment. Dietary habits, study adherence, acceptability of the tablet, and adverse events will be also recorded. After 1 year of treatment, a hand and wrist X-ray will be performed for bone age assessment.

*Evaluation post-treatment (time 2 years):* will include a clinical visit 1 year after treatment discontinuation, collecting the same parameters as at time 0, 6 months, and 1 year; in addition, an abdominal MRI scan and a blood sampling (to assess endocrine-metabolic and inflammation variables and safety markers) will be performed. Dietary habits, study adherence, acceptability of the tablet, and adverse events will be also recorded. Six months later a phone call will be made to ascertain the presence or absence of menarche.

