#### Assessment of outcomes

*Bone age:* A hand and wrist X-ray of the left hand will be taken at the Radiology Department either at HJT or HSJD, at treatment start and after 1 year on treatment. At each center, bone age will be determined with the same BoneXpert programme [version 3; February 2021 (Visiana, Denmark)] [38]. This method will yield bone ages by Greulich & Pyle (GP) and by Tanner-Whitehouse 2 (TW2). Bone age maturation will be annualized by calculating the ratio between the increase of BA over the increase in CA (ΔBA/ ΔCA) [38].

*Clinical characterization:* Clinical variables will be obtained during the clinical visits with the pediatric endocrinologist at HJT and HSJD. The same investigator at each center will assess the clinical variables at times 0, 6 months, 1 year, and 2 years. Halfway the second post-treatment year, the girls will be contacted by phone to discuss the absence or timing of menarche.

*Blood sampling:* 23 mL of peripheral blood in a fasting state will be drawn in the early morning at each clinical center, at baseline (time 0), after 6 months on treatment, after 1 year on treatment, and 1 year off treatment. Blood samples will be stored (at −80 °C) at the Pediatric Endocrinology lab (IDIBGI) and at the Metabolic Endocrinology lab (IRSJD) until analyses.

*Endocrine-metabolic variables analysis:*

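### The blind for families and clinical investigators is guaranteed only to month 24, so the menarche call at month 30 falls outside it

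*Protocol article*

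**What the plan says.** **Length of the phases.** The abstract gives "double-blind treatment: 1 year; open follow-up: 1 year". Trial design {8} says of the period after the treatment year: "After this year, all girls will be followed for 1 year".

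**End of the blind.** Who will be blinded {17a} states: "Study participants and clinically involved investigators will remain blinded until the end of the post-treatment year". The statistical investigators are unblinded sooner, once the on-treatment database is locked. Families who withdraw are told the allocation after an end-of-study visit (Procedure for unblinding {17b}).

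**The menarche contact.** It is described three times:
- Trial design {8}: "Halfway the subsequent year, all girls will be contacted for information on menarche".
- Collection of outcomes, directly after the 2-year visit: "Six months later a phone call will be made to ascertain the presence or absence of menarche".
- Assessment of outcomes: "Halfway the second post-treatment year, the girls will be contacted by phone to discuss the absence or timing of menarche".

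**Status of menarche.** It is absent from the primary and secondary outcomes in Outcomes {12}, where the listed pubertal measure is Tanner stage. It is nevertheless collected under the two outcome-collection headings of section {18a}, and that section closes by saying that all outcomes are compared between the groups at their time points.

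**Concomitant treatment.** Section {11d} prohibits other oral hypoglycemic drugs and other anti-androgens during the trial. It gives no end date relative to month 24 or month 30.

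**The concern.** The trial asks whether treatment slows maturation, and menarche is the last maturation event on which it collects information. The contact is planned for every girl, yet the blind is fixed to end before it.

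Two things could then differ by arm between months 24 and 30. Families or clinicians who know the allocation could act on it, and families could differ in whether they answer the call. The protocol itself makes the first route conceivable. It says of metformin that "its use has significantly increased in younger children and adolescents without diabetes, including for early maturation", and it cites pilot work in which metformin monotherapy could "decelerate the progression of puberty to menarche". If girls from the placebo arm were more likely to start such treatment after disclosure, a difference in menarche would tend to shrink. Non-response that differs by arm could push the comparison either way.

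Reporting bias is the smaller worry. Whether menarche has occurred is a fairly hard fact. Its recalled date, which the call also seeks, is softer.

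**Working it through.** The article gives no figure of its own for this point, so the check is date arithmetic on its stated schedule.

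**Inputs.** Treatment 12 months; post-treatment follow-up 12 months; menarche call 6 months after the 2-year visit; age at start 8.0–9.5 years (Eligibility criteria {10}); recruitment 1 year (abstract); expected start November 2022 and expected completion March 2026 (Trial status).

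1. *End of the guaranteed blind, counted per girl:* 12 + 12 = month 24.
2. *Menarche call:* 24 + 6 = month 30 from Collection of outcomes. Halfway through the second post-treatment year is 12 + 12 + 6 = month 30 from Assessment of outcomes. Trial design {8} gives the same, 24 + 6 = 30. The three descriptions agree.
3. *Interval not covered:* 30 − 24 = 6 months.
4. *Age over that interval:* 8.0 + 2.0 = 10.0 to 9.5 + 2.0 = 11.5 years at month 24; 8.0 + 2.5 = 10.5 to 9.5 + 2.5 = 12.0 years at month 30.
5. *If the end of the post-treatment year is read as one trial-wide date:* the last girl enters by calendar month 12 and finishes that year at 12 + 24 = calendar month 36. A girl enrolled at calendar month r is called at r + 30. She is still covered if r + 30 ≤ 36, that is r ≤ 6. Girls enrolled in the second half of recruitment are called after the blind ends, the last at 12 + 30 = 42, again 6 months late. With even recruitment (an assumption) that is about half of the girls.
6. *Listed outcomes:* the primary outcome covers months 0–12, and the last scheduled measurement of a listed secondary outcome is at month 24. None falls after the guaranteed blind.
7. *Calendar:* November 2022 + 12 months of recruitment + 30 months = May 2026, two months after the expected completion of March 2026. If recruitment takes the full year, the last calls fall after the stated end of the trial. This adds to the doubt about whether restrictions that apply during the trial reach those girls.

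The sample size (21 per arm, raised to 32 for dropout) concerns the month-12 primary outcome and does not change.

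**The case against.** The strongest reply is that no listed outcome is touched. Menarche is in neither outcome list, the specific objectives do not name it, and pubertal tempo is to be judged by Tanner stage. That stands, and it limits the point to a minor one. It does not remove it, because the article collects menarche as outcome information from all girls and says that outcomes are compared between groups.

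Second, a reader might infer that all families are unblinded when called. The text does not say so. Staying blinded until a date permits disclosure then but does not require it, and disclosure is described only for withdrawals. On the trial-wide reading, girls enrolled in the first six months would still be covered.

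Third, a reader might infer that families may freely take the tablet's components after month 24. The documents do not support this either. Section {11d} bars the relevant classes during the trial and is silent on whether months 24–30 count. What can be said is that neither a restriction nor a record of such treatment is clearly stated for those months.

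Fourth, the pilot results on menarche come from 3–4 years of metformin. They do not show that at most six months of late-started treatment would move it. That is also correct, and it is one reason why no size can be given to the bias.

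Finally, the call already asks about timing as well as absence of menarche, so events before month 24 can be dated and separated from later ones, subject to recall. That helps in part.

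**Conclusion.** The point holds as a minor gap in the design. For each girl there are 6 months, from month 24 to month 30, in which menarche information is still to be collected and the blind is not guaranteed. On a trial-wide reading of the blinding sentence the gap remains for girls enrolled in the second half of a one-year recruitment.

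It does not threaten the primary outcome, the listed secondary outcomes to month 24, the sample size or the power. The amount of bias in a menarche comparison cannot be estimated, because the documents give no rate of disclosure at month 24, of new treatment afterwards, or of non-response by arm. The concern assumes only that these are not all zero.

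A related wording should be reconciled. The abstract calls the post-treatment year open, while section {17a} keeps families and clinical investigators blinded through it. The two agree only if open means off study treatment.

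**What to change.** Amend Who will be blinded {17a} so that each girl's family and clinical investigators remain blinded until her month-30 menarche call has been recorded. Tying the end of the blind to that call also settles whether the date is per girl or trial-wide. At the same call, record any new treatment affecting puberty that was started since the 2-year visit. The timing of menarche is already asked there, so no further item is needed for it. Disclosure to families who withdraw can stay as section {17b} has it, and any menarche information from them should be identified as collected after disclosure.

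The cost is that each family and its clinicians learn the allocation about 6 months later. It needs one sentence in the protocol, a matching line in the participant information, and one question at an existing call. No visit is added, and no sample-size or power figure changes.
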